### Statistical analysis

The analysis plan was adopted for a previous RCT on physical activity in diabetes in Oman [36]. Once all participants have been randomised, descriptive statistics including t-test for continuous variables and chi square for binary variables will be used to compare the two group’s variables at baseline. Descriptive analysis will also be used for summary statistics on patient assessment, eligibility, recruitment, withdrawal.

The primary outcome which is the rate of PA and healthy diet score, BMI and glycated hemoglobin over 12 months for all participants in both trial arms at 3, 6, and 12 months will be measured, summarized and tabulated for both study arms. Graphical illustration (box plots, histograms and bar charts) will be used where appropriate and the distributions of all outcome measures will be checked and transformed where appropriate. The main analysis will be linear regression modeling to test the main hypothesis related to the superiority of the proposed intervention in promoting healthy lifestyle compared with control group. All outcomes will be analysed adopting an intention-to-treat principle and all persons will be analysed in the groups to which they were randomised. We will try to minimize missing of data collected by ensuring complete and accurate data entry, however multiple imputation on the longitudinal data will be performed if we face missing data. For secondary analyses, logistic regression will be used adjusting for clustering of patients within health care facilitates.

Analysis and reporting of the results will follow the Consolidated Standards of Reporting Trials guidelines (CONSORT) for reporting RCTs [39]. SPSS version 21 will be used for data analysis.

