### Randomisation

The study is a 1 year 1:1 cluster randomized controlled trial of the lifestyle intervention versus usual care. A cluster randomisation design will be used to minimize between group contamination by having the two groups (intervention and comparison) from independent health centres. Group allocation will be generated using a random numbers table generated in SPSS v21done by an independent statistician at MOH. All health facilities (8) will be randomised to deliver either the intervention (*n* = 4) or usual care (n = 4). Health facilities will be informed of their allocation verbally by the project investigator and will receive an envelope containing invitation letter and project materials.

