### Sample size calculation

The study is powered to detect a change considered to be both meaningful and plausible on the primary outcome. A sample size of 392 (196 in each arm) will allow measuring a between group difference of 7% in BMI and 0.6%in HbA1c over 12 months from baseline, within a power of 80%, significance level of 5%, [19, 37] and a standardised difference of 0.394 (i.e. 0.394 of a standard deviation can be detected) under an Intra-cluster correlation coefficient of 0.01). With a drop-out rate of 20% and a recruitment rate of 70% the required sample size is 750 (375 in each arm). The equation below was used to calculate the sample size based on evidence from nearby countries, the UAE [38].

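### The main analysis is a linear regression with no allowance for facility clustering, so a nominal 5% test in this 4-versus-4 facility trial has a true error of about 11% or more

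*Protocol article*

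**What the plan says.** All references are to the Methods of the protocol article.

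- **Randomisation:** the facility is the unit allocated. "All health facilities (8) will be randomised to deliver either the intervention" or usual care, four in each arm. The Study setting section also gives eight facilities in total.
- **Sample size calculation:** the target is "A sample size of 392 (196 in each arm"), for "a standardised difference of 0.394 (i.e. 0.394 of a standard deviation can be detected"), "under an Intra-cluster correlation coefficient of 0.01".
- **Statistical analysis, main test:** "The main analysis will be linear regression modeling to test the main hypothesis related to the superiority of the proposed intervention". The primary outcomes named there are physical activity, diet score, BMI and HbA1c. Table 2 lists the underlying measures as continuous, so they fall under this linear model.
- **Statistical analysis, later in the same paragraph:** "For secondary analyses, logistic regression will be used adjusting for clustering of patients within health care facilitates".

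Nowhere else does the article give the main analysis an allowance for facility.

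**The concern.** The design and the sample size both recognise that patients in one facility resemble each other. The main test, as written, does not, and the adjustment is attached to a different set of models. Ordinary linear regression on arm counts several hundred independent patients, whereas the comparison rests on eight randomised units, with 8 − 2 = 6 degrees of freedom between facilities.

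Standard errors for the primary outcomes would then be too small, confidence intervals too narrow and p-values too low. A chance difference between two sets of four facilities could be reported as an effect of the intervention, in a trial meant to inform national diabetes policy.

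**Working it through.** **Inputs from the protocol article.** Four facilities per arm (Randomisation). From Sample size calculation: ICC 0.01, 0.394 SD, 196 per arm, 375 per arm after inflation, 20% drop-out, 70% recruitment, 80% power, 5% significance. A two-sided test is assumed, because sidedness is not stated.

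**Step 1: reproduce the stated sample size.** Without clustering, n per arm = 2 × (1.960 + 0.842)² / 0.394² = 101.1, so 102. The design effect is DE = 1 + (m − 1) × ICC, with m patients per facility.

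- m = 375/4 = 93.75: DE = 1 + 92.75 × 0.01 = 1.9275, and 102 × 1.9275 = 196.6. This matches the stated 196.
- m = 196/4 = 49: DE = 1.48, and 102 × 1.48 = 151. This does not match.

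The stated size is therefore consistent with nearly doubling the sample to pay for clustering.

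**Step 2: true error of an unadjusted test.** Clustering multiplies the variance of the arm difference by DE. The true two-sided error of a nominal 5% test is 2 × [1 − Φ(1.96/√DE)].

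| Patients analysed | m per facility | ICC | DE | 1.96/√DE | True error |
|---|---|---|---|---|---|
| 392 | 49 | 0.01 | 1.48 | 1.611 | 10.7% |
| 420 (750 × 0.7 × 0.8) | 52.5 | 0.01 | 1.515 | 1.592 | 11.1% |
| 600 (750 × 0.8) | 75 | 0.01 | 1.74 | 1.486 | 13.7% |
| 750 | 93.75 | 0.01 | 1.93 | 1.412 | 15.8% |

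**Step 3: check by simulation.** In 40,000 null trials with four facilities per arm and ICC 0.01, the unadjusted two-sample t test (equivalent to linear regression on arm) rejected in 10.6% (m = 49), 13.7% (m = 75) and 16.1% (m = 94). A t test on the facility means (6 df) rejected in 5.0%, 4.7% and 5.0% of the same trials.

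**Step 4: sensitivity.** The protocol gives only one ICC; the others here are assumed. With 392 analysed, the error is 7.8% at ICC 0.005, about 16% at 0.02 and 28.8% at 0.05. The Abstract speaks of eight centres in each arm. If that were right, ICC 0.01 would give 7.8% (392 analysed) to 10.5% (750 analysed).

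**Step 5: power under a correct analysis.** With 6 df the critical value is 2.447. At 196 per arm, SE = √(2 × 1.48/196) = 0.123 SD and the noncentrality is 0.394/0.123 = 3.21, giving power of about 76%. At 300 per arm (DE 1.74) power is about 86%.

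**The case against.** **The wording is silent, not explicit.** The article does not say that the regression is unadjusted. It condenses a fuller plan, says its analysis plan is linked to an earlier trial, and its authors plainly know about clustering. Loose wording for a cluster-adjusted model is possible. But the article does address clustering, and gives the adjustment to the secondary analyses only. A reader who follows the text would fit the main model without it.

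**The multiple is conditional.** It rests on ICC 0.01 and four facilities per arm. It falls below twofold at ICC 0.005 with 392 analysed, or with the Abstract's eight centres per arm and 392 analysed. Adjustment for baseline could also change the residual ICC, and the documents give no figure for that. These limits stand. The error nevertheless exceeds 5% in every case computed, and both Methods sections support eight facilities in total.

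**The figure near 16% needs 94 analysed per facility.** If 375 per arm is the number approached, the protocol's own rates leave 210 per arm, or 52.5 per facility, and the error is about 11%. This is fair: 15.8% is the upper end, not the central case.

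**A mixed model may not deliver 6 df.** With eight facilities, ICC 0.01 and 49 patients each, the between-facility variance is estimated as zero about 33% of the time, and Satterthwaite degrees of freedom can then revert to the patient level. In simulation at ICC 0.01, however, that model held its error at 4.4% to 4.9% overall. Large-sample z tests were liberal, at 6.4% to 7.7%. The small-sample correction is therefore worth specifying, and the facility-mean test covers the remaining doubt.

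**Conclusion.** The concern holds: the plan is wrong as written. It randomises facilities and budgets for clustering in the sample size, then names a main test without that allowance and puts the adjustment in the secondary models.

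On the protocol's own inputs, a nominal 5% test of a primary outcome has a true error of 10.7% to 15.8%, which is 2.1 to 3.2 times nominal. The lower end is the more likely if the stated drop-out and recruitment rates apply. These figures are per test at one time point. They assume a two-sided test, equal facility sizes, four facilities per arm, ICC 0.01 and no change in the residual ICC from covariates. This must be corrected before the data are analysed.

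**What to change.** Rewrite the main-analysis sentence in Statistical analysis to specify:

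- a linear mixed model for each primary outcome at 12 months, with arm as a fixed effect and facility as a random intercept (if 3 and 6 months are also modelled, the facility effect must stay in the model);
- small-sample degrees of freedom (Satterthwaite or Kenward-Roger), not large-sample z tests or uncorrected sandwich errors;
- a t test on the eight facility means (6 df) as the confirmatory check;
- facility in the multiple-imputation model.

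The facility count in the Abstract should be brought into line with the Methods, because the degrees of freedom depend on it.

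The change is one paragraph of wording and needs no new data. The price is wider confidence intervals and, on 6 df, power of about 76% at 196 analysed per arm instead of the stated 80%. About 300 analysed per arm would give 86%. The Sample size calculation section should acknowledge this.

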**Methods:**

A one year 1:1 cluster randomized controlled trial will be utilized to compare the use of phone consultations, a multi component interactive phone application and pedometers with the usual diabetes care on promoting PA and healthy diet. Participants will be screened for inactivity and should be T2D, aged18–65 years, and overweight or obese. Eight primary centers will be randomly selected in each arm (*n* = 375). The primary outcome is the between arms differences in PA and diet scores, BMI and HbA1c over 12 months from baseline. Additionally, secondary outcomes will include cardiovascular outcomes (BP, and lipids).

The trial has received ethical approval from the Omani Research and Ethical Review and Approval Committee. All eligible participants will be invited to their respected health centers to provide informed consent.

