**Secondary Outcomes**			
**Socio-demographic data**	**Questionnaire**	**B**	**Binary / numerical**
**Height (m)**	**Stadiometer**	**B**	**continuous**
**Pedometer**	**Reporting step counts**	**B, 3F, 6F, 12F**	**numerical**
**GPAQ-MET-mins/week**	**Questionnaire**	**B, 3F, 6F, 12F**	**continuous**
**Diet assessment tool**	**Questionnaire**	**B, 3F, 6F, 12F**	**continuous**
**Lipid profile (mmol/l)**	**Blood test (venous fasted sample)**	**B, 3F, 6F, 12F**	**continuous**
**Blood pressure (mmHg)**	**Sphygmomanometer**	**B, 3F, 6F, 12F**	**continuous**
**Exit survey**	**Questionnaire (participants and project officers)**	**12F**	**description**

(B = baseline; 3F = 3 month follow-up; 6F = 6 month follow up; 12F = 12 month follow-up)

^a^while blood collection for HbA1c at 12 month is mandatory, it is only done at baseline, 3 and 6 month if missing from the electronic health information system or recorded within more than 4 months prior to the measurement visits

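### Logistic regression is the only method named for secondary analyses, although blood pressure, lipids and step counts are typed continuous or numerical and no cut-off is defined for any of them

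*Protocol article*

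**What the plan says.** The Statistical analysis section assigns methods in two sentences. For the main hypothesis: "The main analysis will be linear regression modeling to test the main hypothesis". For everything secondary: "For secondary analyses, logistic regression will be used adjusting for clustering of patients within health care facilitates". No other model is named, and no covariates are listed for either.

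The Abstract says that "secondary outcomes will include cardiovascular outcomes (BP, and lipids" (blood pressure and lipids). Table 2 types both as continuous and step counts as numerical, all measured at baseline, 3, 6 and 12 months. Under the same secondary heading it lists "GPAQ-MET-mins/week" and "Diet assessment tool", also as continuous.

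The Secondary objectives add change in physical activity and sitting time, kidney-function tests, retinopathy, foot findings and the course of drug treatment. Neither Table 2 nor the text gives a threshold or responder definition for any quantitative outcome.

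On the primary comparison the Abstract says: "The primary outcome is the between arms differences in PA and diet scores, BMI and HbA1c over 12 months from baseline".

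**The concern.** Logistic regression needs a categorical response. To apply it to blood pressure in mmHg or lipids in mmol/l, someone must first choose a cut-off. The article gives none, so the choice would fall to the analyst, possibly with the data in view. The effect would then be an odds ratio for an undefined event instead of a difference in means, estimated with less information.

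The labelling conflict widens the problem. Physical activity and diet are primary in the Abstract, in the Primary outcome section and in Statistical analysis, but secondary in Table 2. Change in physical activity also appears among the Secondary objectives. On one reading these scores get linear regression, on the other logistic.

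A related matter is precision. Table 2 collects a baseline value of every outcome discussed here, but the analysis text does not say whether the models use it.

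**Working it through.** **1. Method against outcome type**

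| Outcome | Type | Binary definition | Method as written |
|---|---|---|---|
| Blood pressure, lipids | continuous (Table 2) | none | logistic |
| Step counts | numerical (Table 2) | none | logistic |
| GPAQ, diet score | continuous (Table 2) | none | linear if primary, logistic if secondary |
| Sitting time, kidney function | no type given; quantitative by nature | none | logistic |
| Retinopathy, foot findings | no type given; categorical by nature | natural | logistic, which fits |

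**2. What a cut would cost (illustration; the plan states no cut)**

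For a normal outcome and a small effect, a cut leaving a proportion p on one side keeps the fraction φ(z_p)² / [p(1−p)] of the information from independent observations.
- Median: 0.399² / 0.25 = 2/π = 0.64.
- 80th percentile: 0.280² / 0.16 = 0.49.

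To express this as power I borrow the Sample size calculation inputs: difference 0.394 SD, 5% (taken as two-sided), 80% power, ICC 0.01, 196 per arm. These were set for the primary outcome and serve only as a yardstick.

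*Reproducing the plan's figure.* 2(1.960 + 0.842)² / 0.394² = 101.1, so 102 per arm. With the enrolled cluster size 375/4 = 93.75, the design effect is 1 + 92.75 × 0.01 = 1.9275, and 102 × 1.9275 = 196.6, close to the stated 196. The analysed cluster size is 196/4 = 49, with design effect 1 + 48 × 0.01 = 1.48. I use 49, and four facilities per arm as in the Randomisation section (the Abstract reads as eight per arm).

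*Kept continuous.* SE = √(2 × 1.48/196) = 0.123; 0.394/0.123 = 3.21; power = Φ(3.21 − 1.96) = 89%.

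*Split at the median.* The proportions are Φ(±0.197) = 0.578 and 0.422, a difference of 0.156.
- Same design effect: SE = √(2 × 0.578 × 0.422 × 1.48/196) = 0.0607; ratio 2.57; power about 73% (72% with the pooled null variance).
- The ICC of a split normal outcome is smaller: (2/π) arcsin(0.01) = 0.0064, so the design effect is 1 + 48 × 0.0064 = 1.31. Then SE = 0.0570, ratio 2.74, power about 78%. Retained information is 0.637 × 1.48/1.31 = 0.72.

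A median split would therefore keep roughly 64% to 72% of the information, and power would fall from 89% to between 72% and 78%.

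**3. What baseline adjustment would gain**

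Let r be the baseline-to-follow-up correlation. The documents give no value, so r is assumed. In units of the follow-up variance, with equal variances at both visits and the same r between and within facilities, the factors are 1 (follow-up only), 2(1 − r) (change score) and 1 − r² (baseline-adjusted). Adjusted against change is (1 − r²)/[2(1 − r)] = (1 + r)/2.

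| Assumed r | Adjusted vs follow-up only | Adjusted vs change score |
|---|---|---|
| 0.5 | 0.75 | 0.75 |
| 0.7 | 0.51 | 0.85 |
| 0.8 | 0.36 | 0.90 |

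At r = 0.7 the variance reduction is thus 49% or 15%, depending on which unadjusted analysis is meant.

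**4. Few facilities**

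Eight facilities in two arms leave 8 − 2 = 6 degrees of freedom between facilities. The two-sided 5% critical value is 2.45 instead of 1.96. On that reference, power at 0.394 SD and 196 per arm is 76% without adjustment and 87% with adjustment at r = 0.5. Adjustment helps, but the correction cannot be left out.

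**The case against.** The best defence has four parts.

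- **Logistic regression has proper uses here.** Retinopathy, foot findings and perhaps treatment course are categorical. This stands, and a reader who infers that logistic regression is wrong for every secondary outcome goes too far. But no other method is named for the quantitative ones. The plan to check and transform the distributions of all outcomes hints at continuous analysis, yet it does not supply a model.
- **Physical activity and diet are really primary.** Most of the article says so, and the linear model follows directly after them. This largely stands, so the firm cases are blood pressure, lipids and step counts.
- **No split is announced.** Also true. The 64% describes one hypothetical cut and is not a loss the plan has committed to. Nor do the documents show that thresholds would be chosen after seeing data; they only leave that open.
- **Baseline may already be used.** A reader might infer from the bare mention of linear regression that baseline is ignored. The documents do not support that. They list no covariates and exclude none, and the Abstract's definition of the primary comparison, like the Sample size calculation, may well mean change from baseline. Covariate lists are also commonly left to a fuller plan. Baseline adjustment is therefore a recommendation here, not the correction of a stated error.

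**Conclusion.** The mismatch holds. The only method named for secondary analyses does not fit blood pressure, lipids or step counts as Table 2 types them, and no binary definition bridges the gap. For physical activity and diet it applies only if Table 2's labelling is followed.

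The size depends on the cut chosen: about 64% of the information kept at the median with independent patients, up to 72% with the smaller ICC of a split outcome, and less at a more extreme cut. These figures assume normality and the sample-size inputs.

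The stronger claim, that the main model discards baseline and so loses precision, is not established. What can be said is conditional: adjustment multiplies the variance by 1 − r² if follow-up values alone were meant, and by (1 + r)/2 if change scores were meant, with r assumed. It improves precision on either reading.

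**What to change.** Replace the sentence on secondary analyses with wording to this effect:

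- Every continuous outcome, primary or secondary, is analysed with a linear mixed model containing arm, that outcome's own baseline value and a facility random intercept, with a small-sample degrees-of-freedom correction (for example Satterthwaite or Kenward-Roger) for eight facilities. The effect is reported as an adjusted mean difference at 12 months.
- Logistic regression adjusted for clustering is kept for outcomes that are binary by nature, such as retinopathy or foot findings, with each event defined.

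Make Table 2, the Abstract and the Primary outcome section agree on whether physical activity and diet are primary. State whether step counts are reported in both arms, since the Pedometer section sits among the intervention components; a between-arm model needs both.

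The cost is a few sentences, slightly more analysis work and the degrees-of-freedom correction. No new data are needed, because Table 2 already schedules these outcomes at baseline.

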### Assessment of fidelity to protocol

Monthly meetings will be conducted to discuss issues regarding the consultations, and measurements to ensure their compliance to intervention protocol.Attendance sheets will be reviewed and discussed.Crosschecking of 10% of phone PA consultation notes randomly selected by a recruited external assessor.

### Stakeholder involvement

At the beginning of the trial a meeting will be held with all Head of health facilities to discuss the practicalities of this intervention. Required approvals will also be sought from the director general of health services, Muscat. A monthly meeting and regular telephone messages with all the project officers will be conducted to facilitate smooth running of the project.

### Participant and public involvement

We will involve 2 to 3 patients with diabetes to share their perceptions and ideas about the practicality of using electronic applications in promoting healthy lifestyle. They are welcomed to join the study team meeting and discuss app components and outcome measures. The perspectives of caregivers will also be taken into consideration in testing and refining the study materials and procedures. At the end of the study, participants and care givers satisfaction with the intervention, including burden, will be assessed as part of the process evaluation.

Results of the main trial and other evaluation findings will be submitted for publication in international peer-reviewed journals and presented at international and regional scientific conferences and webinars.

Furthermore, the findings will be shared to the community through social media platforms to encourage community engagement in healthy lifestyle promotion.

## Discussion

Globally 72% of deaths are attributed to NCDs (4% due to diabetes vs 8% in Oman). Governments including Oman have endorsed nine global voluntary targets to reduce premature death from the four major NCDs (cardiovascular, diabetes, respiratory and cancer) by 25% by 2025 [40]. This project is targeted towards facilitating the global aims of: A) 25% relative reduction in the overall mortality from cardiovascular diseases, cancer, diabetes, or chronic respiratory diseases, B) 10% relative reduction in prevalence of insufficient physical activity and C) 80% availability of the affordable basic technologies and essential medicines required to treat major NCDs.

Oman has been chosen as one of the 12 countries to be monitored for combating NCDs and their risk factors including UN declaration 2011 for NCDs. In response, several strategic actions were put in place:
Launching the national policy for prevention and control of NCDsOman health vision 2050 including NCDsMinistry of health policies and national five health development plansThe Oman national policy for diet and physical activity and healthThe national NCDs screening program

To the best of our knowledge, this is the first study in Oman exploring the implementation/integration of lifestyle intervention methods within routine diabetes health care facilities. This proposal (longitudinal cluster randomised trial) meets the aim of the strategic research program for NCDs through providing:
Data on levels of physical behaviour including sedentary time in adults with diabetes.Building partnership with other educational, governmental and organisations to promote healthy lifestyle.Evidence on ways for implementation, up scaling and roll out of the intervention to other regions in Oman.Opportunities for updating the current diabetes management policies and guidelines to meet the actual clinical needs.

